#### Analysis of secondary outcomes

Continuous secondary outcomes assessed at multiple follow-up time points will be assessed using linear mixed models. As for the primary binary outcomes, the repeated measures of each outcome at baseline, 2 weeks, 4 weeks, 8 weeks, and 3 months follow-up as the dependent variable, with follow-up timepoint as level 1, participants as level 2, and GPs as level 3. Timepoint and an interaction between treatment allocation and time points will be included as independent variables. Treatment allocation will not be included as a separate main independent variable as recommended by Twisk et al. (2018).

Continuous and binary outcomes measured at baseline and once during the follow-up period will be analyzed using linear or logistic regression, respectively. For each outcome, the follow-up measurement will be included as the dependent variable, with treatment allocation as the primary independent variable of interest. These analyses will also be adjusted for the baseline value of the outcome variable and possible prognostic variables (e.g., age, sex, education, and pain-duration). These analyses will include only participants who have completed both the baseline and 3-month follow-up questionnaires. We have not planned any imputation of missing data for these secondary outcomes.

Details of the analyses will be published in the statistical analysis plan. Stata/MP v17.0 will be used to all statistical analyses (College Station, Texas, USA).

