### Eligibility criteria {10}

Inclusion criteria are age 18 or older who make appointment with their GP due to MSK pain complaints in the neck, shoulder, low back, hip, knee, or multisite pain. Patients with both acute and chronic pain can be study participants. Exclusion criteria are reduced cognitive function, specific diagnoses such as fractures, neurological conditions (i.e., stroke, multiple sclerosis, etc.), planned surgery related to the MSK pain complaint, or surgery or fracture related to the MSK pain complaint the last 6 months, active cancer disease, pregnancy-related disorders, and poor comprehension of Norwegian language. GPs participating in the study must be a part of the Norwegian publicly funded regular GP scheme (“Fastlegeordningen”).

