#### Medication relevant for musculoskeletal pain complaints

The recommendation for use of medication was based on the NICE guidelines for treatment of MSK pain complaints, expert consensus groups, and literature review. The recommendation differentiates between phenotype 1–3 and 4–5 (Additional file 2). The rationale for this differentiation is that the duration of pain differs the most between these two groups [28] and that participants with a long-lasting pain may benefit from a different approach than participants experiencing acute pain. All recommendations are graded as “could be considered” or “only if specific indication,” i.e., yellow or red. This is because the use of painkillers in the treatment of MSK pain complaints in general should be limited and very rarely is used as sole treatment, but rather to support other treatment options, e.g., physiotherapy, exercise, and lifestyle changes [32].

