#### Analysis of the primary outcome

The effect of CDSS at 3 months will be estimated for both primary outcomes using three-level mixed logistic regression models. Each primary outcome will be assessed in a separate model that includes the repeated measures of the outcome at 2 weeks, 4 weeks, 8 weeks, and 3 months follow-up as the dependent variable and such that they are clustered by follow-up timepoint (level 1), participants as level 2, and GPs as level 3. Treatment allocation, time point, and an interaction between treatment allocation and time point will be included as independent variables. We will adjust for the stratification variable and possible prognostic variables (age, sex, education, and pain-duration). In addition, when analyzing PSFS, we will adjust for the baseline value.

The treatment effect will be estimated for each time point from the mixed logistic regression models and presented as an OR with 95% confidence intervals.

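### The mixed model for repeatedly measured continuous outcomes names no prognostic covariates, so an arm difference in pain duration would be only partly corrected in the 3-month pain effect (minor)

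*Protocol article*

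**What the plan says.** In the protocol article, Analysis of secondary outcomes, the linear mixed model for continuous outcomes with several follow-ups takes "the repeated measures of each outcome at baseline, 2 weeks, 4 weeks, 8 weeks, and 3 months follow-up as the dependent variable". Its terms are then listed: "Timepoint and an interaction between treatment allocation and time points will be included as independent variables". The section adds that "Treatment allocation will not be included as a separate main independent variable", so both arms share one baseline mean. No prognostic covariate is named.

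The other two model families do name covariates:

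- Analysis of the primary outcome: "We will adjust for the stratification variable and possible prognostic variables (age, sex, education, and pain-duration".
- Analysis of secondary outcomes, on outcomes with one follow-up: "These analyses will also be adjusted for the baseline value of the outcome variable and possible prognostic variables", with the same four variables given as examples.

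Among the listed secondary outcomes, pain intensity clearly belongs to the repeated-measures model: Table 2 marks it at baseline and weeks 2, 8, 12 and 26. EQ-5D and MSK-HQ are collected at baseline and weeks 12 and 26, and would join it only if week 26 is modelled.

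**The concern.** Pain duration may well predict how pain changes, not only how high it starts. Under Eligibility criteria {10}, "Patients with both acute and chronic pain can be study participants". The medication section separates phenotypes 1–3 from 4–5 because "the duration of pain differs the most between these two groups", and Background and rationale {6a} reports different recovery trajectories across the phenotypes. Two patients with the same baseline score may therefore follow different courses.

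Randomising GPs does not guarantee that the recruited patients are alike. GPs are unblinded (Who will be blinded {17a}), are already allocated when patients enrol (Participant timeline {13}), and identify the patients who are invited (Who will take informed consent? {26a}). If the mix of acute and chronic pain came to differ between arms, part of that difference would appear as a treatment effect on pain. The pain result would also be adjusted differently from the primary results it is read beside, with no reason given.

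**Working it through.** **The plan's own figure.** No figure is stated for the pain model. The sample size for the primary outcome reproduces and supplies the design inputs. Detecting 50% versus 65% with two-sided alpha 0.05 and 80% power needs 170 per arm before clustering. The design effect is 1 + (14 − 1) × 0.05 = 1.65, and 170 × 1.65 = 280.5, against the stated 280 per arm in 20 GPs.

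**Inputs.** From the protocol: 20 GPs per arm, 14 patients per GP, ICC 0.05. Assumed, because the documents give none: NRS standard deviation 2.5 (or 2.0); baseline to 3-month correlation 0.5; arm difference D in the share with long duration of 0.10 (or 0.20); effect of long duration on 3-month pain b_t = 1.0; effect on baseline pain b_0 = 0 or 0.5.

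**Shift left in the 3-month effect.** With a shared baseline mean, the model behaves approximately like an adjustment for baseline pain:

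shift = D × (b_t − slope × b_0), with slope 0.5.

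- D = 0.10, b_0 = 0.5: 0.10 × (1.0 − 0.25) = 0.075.
- D = 0.10, b_0 = 0: 0.10 × 1.0 = 0.10.
- D = 0.20: 0.15 and 0.20 respectively.

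The shared baseline therefore removes about a quarter in the first case and nothing when duration is unrelated to baseline pain.

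**Standard error.** SE = SD × √(2 × 1.65 / 280) × √(1 − r²). For SD 2.5 and r = 0.5 this is 2.5 × 0.1086 × 0.866 = 0.235; for SD 2.0 it is 0.188.

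**False-positive rate.** P(|N(shift/SE, 1)| > 1.96):

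- 0.075 / 0.235 = 0.32, giving about 6.2%.
- 0.10 / 0.235 = 0.43, giving about 7.1%.
- 0.10 / 0.188 = 0.53, giving about 8.3%.

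**Which adjustment repairs it.** A simulated three-level model used four time points, the design above, SD 2.5, variance components treated as known and 800 repetitions (Monte Carlo error about 0.198/√800 = 0.007). With D = 0.10, the mean shift at 3 months was:

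| Duration effect on baseline pain | No covariate | Main effect only | Covariate × time |
|---|---|---|---|
| 0.5 | 0.073 | 0.040 | 0.002 |
| 0 | 0.094 | 0.082 | −0.002 |

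A main effect is one constant across all time points. Here baseline is one of those points, so that constant cannot describe an effect on change. The primary and single-follow-up models have only follow-up values as the outcome, so a main effect suffices there.

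**Precision with balanced arms.** The proportional gain in SE is 1 − √(1 − R²), where R² is what the covariates explain beyond baseline pain: 0.5% at R² = 0.01 and 5.1% at R² = 0.10. In the simulation without imbalance the SE was 0.195 to 0.202 without the covariate and 0.189 to 0.193 with covariate × time.

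**The case against.** The strongest reply is that this is a condensed article. The section introduces the model by likening it to that for the primary outcomes and leaves details to a statistical analysis plan that is not shown. The covariates might carry over, and the text nowhere says the model is unadjusted. This stands in part: it is not proof that the final analysis will be unadjusted. But the comparison introduces the repeated measures and the levels, after which the section lists the model's terms itself and states deliberately which term is left out. An analysis built as written omits the covariates. If they did carry over as in the primary models, they would be main effects, which repair little here.

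The second reply is that selection is possible but not shown. Patients receive a standard electronic message, screen themselves, consent online without the GP, and do not know the arm at baseline. That stands. The imbalance and the strength of the duration effect are assumptions, and without imbalance the model is valid.

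A reader might also infer more than the documents support:

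- That an imbalance would go wholly uncorrected. The shared baseline mean already takes out whatever baseline pain carries.
- That false positives reach 10–14%. That takes a duration effect of up to 1.5 points, no link between duration and baseline pain, and a smaller SE from GP, patient and residual variances of 0.15, 2.3 and 2.3 (ICC 0.15/4.75 = 0.03, not the protocol's 0.05) and 44 × 14 = 616 analysed patients, against the 560 that the protocol counts after drop-out.
- That much precision is lost. Baseline pain already supplies most of what adjustment can give.

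**Conclusion.** The point holds as a minor inconsistency with a cheap remedy. The stated terms of the repeated-measures linear model omit covariates that the other two model families include, and the design leaves room for an arm difference in the one covariate most likely to matter. Under a 10-point imbalance and a 1.0-point duration effect, the remaining shift is about 0.07 to 0.10 NRS points, roughly a third to a half of a standard error, and the false-positive rate is roughly 6–9%. A 20-point imbalance would about double the shift; none would leave no bias and only a few percent of SE to gain. All of these rest on assumed values. The consequence is confined to pain intensity, and to EQ-5D and MSK-HQ if week 26 is modelled. The primary outcomes are not affected.

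**What to change.** In Analysis of secondary outcomes, add age, sex, education and pain duration to the linear mixed model for repeatedly measured continuous outcomes, each with an interaction with time. Separating baseline from follow-up is the minimum; a term at each time point is safer if the effect of duration grows over follow-up. If parameters must be saved, pain duration is the interaction to keep. Settle this before unblinding, so that the choice of adjustment cannot depend on the results.

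The cost is one sentence and a few extra parameters, using variables the protocol already plans to adjust for elsewhere. Adjustment will not remove selection on factors that are not measured.

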### Trial design {8}

The study will be a multicenter, cluster-randomized, controlled trial. GPs are the clusters, and each GP will be randomized to one of the two groups, i.e., current care with or without the CDSS for stratified care intervention. The allocation ratio is 1:1. The protocol is reported according to the Standard Protocol Items: Recommendations for interventional Trial statement [29].

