#### Sample size {14}

Sample size calculations based on the *clustersampsi* command in Stata for cluster-randomized, controlled trials show that 280 participants and 20 clusters (GPs) are necessary in each arm to detect a difference of 15% in proportions of participants “improved.” These calculations are based on a power of 80%, alpha level of 0.05, intra-class correlation coefficient (ICC) of 0.05, and an average cluster size of 14 participants per GP. Suggestive values for ICC were obtained from a previous project in primary care, and the same data suggest that the proportion of participants reporting “improved” after usual care physiotherapy was 50–58% in the target groups. To account for a 15–20% drop-out among the participants and 5–10% among the GPs, we will include 22 GPs in each arm and 17 participants in each cluster, giving a total of 748 participants.

Sample size calculations determined that fewer participants would be required to achieve 80% power when assessing the proportion of participants who experience a clinically important improvement in their functional status at each follow-up time point using a mixed logistic regression model, and the above sample size calculation therefore was used to determine the required number and size of clusters.

The two primary outcomes will be analyzed by multilevel modeling to account for clustering of individual data and adjust for covariates. A detailed statistical analysis plan will be published before unblinding of study data.

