### Statistical methods

#### Statistical methods for primary and secondary outcomes {20a}

We will publish a detailed statistical analysis plan in the ISRCTN registry. The statistical reporting will adhere to the CONSORT statement, including the extension to cluster randomized trials [37, 38]. We will describe GP characteristics as follows sex, age, location (rural/urban areas), years of working in general practice, specialist status, and number of patients under their care. We will also describe participant demographics, including sex, age, and education level to avoid selection bias.

The primary analyses for the primary and secondary outcomes will be intention to treat.

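### Secondary outcomes with a single follow-up are assigned to linear or logistic regression with no GP term, although GPs are the unit of randomisation, and no binary secondary outcome has a clustered model

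*Protocol article*

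**What the plan says.** Under Trial design {8} the protocol article is explicit about the unit of randomisation: "GPs are the clusters, and each GP will be randomized to one of the two groups". The Sample size section {14} allows for this with an "intra-class correlation coefficient (ICC) of 0.05, and an average cluster size of 14 participants per GP". That section promises multilevel modelling for the two primary outcomes, and the primary-outcome section specifies it: three-level mixed logistic models with GP as the top level.

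The section on analysis of secondary outcomes has two routes:

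- **Continuous outcomes with several follow-ups.** These go to a linear mixed model with time point, participant and GP as its three levels. The times listed run from baseline to 3 months.
- **Outcomes with one follow-up.** "Continuous and binary outcomes measured at baseline and once during the follow-up period will be analyzed using linear or logistic regression, respectively". The terms are allocation, the baseline value, and prognostic variables such as age, sex, education and pain duration. The analysis set is fixed as well: "These analyses will include only participants who have completed both the baseline and 3-month follow-up questionnaires".

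No GP term or clustered variance estimator appears on the second route. The section ends by leaving details to the statistical analysis plan, which is not shown.

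**The concern.** Patients of the same GP share that GP's allocation and habits, so their outcomes are likely to be correlated. A regression that treats them as independent takes its precision from the number of patients, although the information on the treatment contrast is limited by the number of GPs. Standard errors come out too small, confidence intervals too narrow and p-values too low.

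The outcomes at stake bear on a main hypothesis of the trial: more adequate care, less overtreatment and lower health care spending. Referral, imaging and number of treatments are largely the GP's own decisions. Appreciable correlation within GP is therefore plausible for them, although the article gives no figure.

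The article is not simply silent here. It names a model, its covariates and its analysis set, directly after a paragraph that does include the GP level. Elsewhere (primary analysis, subgroup analyses, missing data) it calls its models mixed when it means mixed.

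**Working it through.** **1. Which outcomes fall under the single-follow-up sentence?** The Secondary outcomes section names eight outcomes. Set against Table 2 and the Data management section:

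| Outcome | Follow-ups | Route if the horizon is 3 months | Route if week 26 counts |
|---|---|---|---|
| Pain NRS | weeks 2, 8, 12, 26 | mixed model with GP level | mixed model with GP level |
| EQ-5D, MSK-HQ | weeks 12, 26 | regression, no GP term | could be the mixed model |
| Painkiller use, sick leave | weeks 12, 26 | regression, no GP term | mixed model only if continuous; if binary, no route is stated |
| Number of treatments, referral, imaging | not in Table 2; GP case report at baseline and 3 months | regression, no GP term (by inference) | unchanged |

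The section's own wording favours the 3-month horizon: the mixed model's time points stop at 3 months, and the regression requires the 3-month questionnaire. On either reading the mixed-model paragraph covers continuous outcomes only, so no binary secondary outcome has a clustered model.

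**2. Reproduce the plan's sample size, to confirm how it treats clustering.** Inputs from Sample size {14}: "These calculations are based on a power of 80%, alpha level of 0.05" (taken as two-sided), ICC 0.05, 14 per GP, a 15-point difference, and a control proportion of 50% from the stated 50–58%.

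- Unclustered n per arm for 50% v 65%, pooled-variance formula: [1.96 × √(2 × 0.575 × 0.425) + 0.8416 × √(0.50 × 0.50 + 0.65 × 0.35)]² / 0.15² = 169.3.
- Design effect: 1 + (14 − 1) × 0.05 = 1.65.
- 169.3 × 1.65 = 279.4 participants; 279.4 / 14 = 19.95 GPs.

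This agrees with the stated "280 participants and 20 clusters (GPs) are necessary in each arm to detect a difference of 15% in proportions". The design therefore rests on a variance inflation of 1.65.

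**3. Effect of leaving the GP out of the analysis.** For an arm-level comparison with equal cluster sizes:

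- Model SE / true SE = 1/√DE = 1/√1.65 = 1/1.285 = 0.778, so the SE is about 22% too small.
- Type I error = 2 × [1 − Φ(1.96/√DE)] = 2 × [1 − Φ(1.526)] = 12.7%.
- Coverage of a nominal 95% interval = 100% − 12.7% = about 87%.

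Simulation under no effect (20 GPs per arm, 14 participants each, 20,000 replicates) gave 12.9% for a continuous outcome and 12.6–12.8% for binary outcomes. A cluster-level t-test on the simulated continuous outcome, over ICCs from 0.01 to 0.10, gave 4.9–5.2%.

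**4. Sensitivity to the ICC, at 14 per GP.** The article gives no ICC for any secondary outcome, so every row is an assumption.

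| ICC | Design effect | Model SE / true SE | Type I error |
|---|---|---|---|
| 0.01 | 1.13 | 0.94 | 6.5% |
| 0.02 | 1.26 | 0.89 | 8.1% |
| 0.05 | 1.65 | 0.78 | 12.7% |
| 0.10 | 2.30 | 0.66 | 19.6% |

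With 17 per GP, the recruited number, and ICC 0.05, the design effect is 1.80 and the error 14.4%.

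**The case against.** **The analysis plan may supply the adjustment.** The article is condensed, does not rule out GP-clustered standard errors, cites the CONSORT extension for cluster trials, and defers details. This stands to the extent that the inflation is conditional on no adjustment being added. It does not clear the text: the article states a model with its terms, and that model, followed as written, ignores the unit of randomisation. The CONSORT citation concerns reporting and names no method.

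**The ICC is borrowed.** The 0.05 is a planning value for the proportion improved. Adjustment for baseline and prognostic factors may lower the residual ICC of the secondary outcomes. This stands, and 12.7% is an illustration at the plan's own value. Even at ICC 0.01 the error exceeds 5%.

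**Stronger readings that the article does not support.**

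- A reader might infer that every secondary outcome except pain is certain to be analysed without clustering. That holds only on the 3-month horizon, and for number of treatments, referral and imaging only by inference. If week 26 counts as a second follow-up, EQ-5D and MSK-HQ could go to the mixed model.
- A reader might see the restriction to completers as contradicting "The primary analyses for the primary and secondary outcomes will be intention to treat". It is an openly stated complete-case choice. Intention to treat can be read there as analysis by allocated arm, and the matter is separate from clustering.
- A reader might conclude that EQ-5D and MSK-HQ must be remodelled over baseline, 12 and 26 weeks. That is a design preference and is not needed to correct the standard errors.

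**Conclusion.** The point holds for secondary outcomes measured at baseline and once in follow-up, and for all binary secondary outcomes: the stated regression has no GP term in a GP-randomised trial. On the 3-month horizon this covers EQ-5D, MSK-HQ, painkiller use and sick leave, and by inference number of treatments, referral and imaging. The article leaves the status of EQ-5D and MSK-HQ open, because both are also collected at week 26.

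The size rests on three assumptions: that no clustering adjustment is added elsewhere, that the secondary outcomes share the planning ICC of 0.05, and that about 14 participants per GP are analysed. The nominal 5% test then runs at about 12.7%. The direction is the same for any positive ICC. Both primary outcomes have GP as a model level, so their analyses and the sample size are unaffected.

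**What to change.** Amend the single-follow-up paragraph, and carry the same wording into the analysis plan:

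1. For every single-follow-up and every binary secondary outcome, specify either a GP random intercept (mixed linear or mixed logistic regression) or GEE or GP-clustered standard errors. With only about 40 analysed to 44 recruited clusters, a small-sample correction should be named with the GEE or clustered-variance option.
2. List each secondary outcome with its type, its analysis time point and its model. State whether week 26 counts as a follow-up for this purpose, so that EQ-5D and MSK-HQ are clearly placed, and name the model for number of treatments, referral and imaging.

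This changes wording only. Data collection, sample size and the primary analyses stay as they are. The one cost is wider confidence intervals for these outcomes: at ICC 0.05 and 14 per GP, by a factor of about 1.28 (√1.65), which is the correct width under those assumptions.
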